### Interval FIT Hb analysis

Fecal Hb analysis in the interval between the delayed colonoscopies for participants randomized to the intervention arm will be performed using two-sample OC-sensor FIT. Testing kits will be provided to participants by mail, with instructions for collection as previously described [36]. Participants will be asked to return the collected fecal samples in the FIT collection devices by mail, within 2 weeks of the first fecal sample being collected. Assessment of fecal Hb concentrations will be performed as per the manufacturer instructions [36]. In the event the FIT result is positive (over 20 µg Hb/g feces or 100 ng/mL of OC-sensor sample buffer in either fecal sample), the surveillance colonoscopy will be scheduled as soon as possible, and the delayed procedure date will be abandoned. These participants will remain enrolled and complete the follow-up survey as dictated in the study schedule.

### Colonoscopy procedure

Colonoscopies will be scheduled within participating institutions across South Australia (Flinders Medical Centre, Noarlunga Hospital, Tennyson Centre Day Hospital, Finders Private Hospital) and will be conducted according to best practice and accreditation requirements at the time. Patients will undergo bowel preparation prior to the procedure (using the preparation and following the instructions specific to each hospital or proceduralist), and the quality of the bowel preparation will be evaluated using the BBPS (Boston Bowel Preparation Scale [37]) with maximum scores of right colon = 3, transverse colon = 3, and left colon = 3, with the total BBPS score equaling 9. Any procedures with a poor bowel preparation, defined as a score of less than 2 in any segment or defined as “poor” in the colonoscopy report, an incomplete intubation, or non-removal of a polyp, will be considered an inadequate incomplete colonoscopy and will be excluded from data analyses. The participant will be scheduled a new procedure date within 6 months of the study colonoscopy procedure date. If the repeat procedure is not completed within 6 months of the study colonoscopy date, the data are excluded from the outcome analysis. The rate of poor bowel preparation (a quantitative BBPS score of less than 2 in any segment, or a qualitative bowel preparation report of “poor”) in the SCOOP program is approximately 5%, which is within the Australian National Health and Medical Research council recommendation of 10% for colonoscopy key performance indicators [15]. If more than 10% of colonoscopy procedures are being excluded due to poor bowel prep, recruitment of participants will continue until the minimum required sample size has been met. The colonoscopy will be performed by trained endoscopists and under anesthesia or sedation. After informed consent is documented, the scope is passed under direct vision with the patient’s pulse and oxygen saturations monitored throughout. The colonoscope is introduced through the anus and advanced to the cecum, which can be identified by the appendiceal orifice and ileocecal valve. Scope withdrawal time is recorded from cecum to rectum. Polyp findings from the colonoscopy are recorded including the Paris classification, location, size, and resection type.

Clinicopathological findings at colonoscopy will be categorized into the following groups: normal, non-neoplastic outcomes, non-advanced adenoma, advanced adenoma, high- or low-risk sessile serrated lesions, or CRC. An advanced adenoma is defined as having any combination of the following features: villous changes, ≥ 10 mm in size, high-grade dysplasia, and traditional serrated adenoma. High-risk sessile serrated lesions are defined as those with dysplasia and/or ≥ 10 mm in size. Non-advanced adenomas and low-risk sessile serrated lesions will be defined as precursor adenomas that do not fit the advanced adenoma or high-risk sessile serrated lesion criteria. Non-neoplastic findings will include hyperplastic polyps, diverticular disease, hemorrhoids, and angiodysplasia, and absence of pathology will be defined as a normal outcome.

### Survey completion

All participants will be mailed paper copies of the surveys for completion, at the timing interval specified in the study schedule (Table 1). Reminder phone calls will be made 4 weeks after the mailing date to ensure compliance with survey completion. Participants are asked to complete the questions to the best of their ability. Survey response will be manually entered into a central computer database.

### Outcome parameters (endpoints)

Primary outcome:Incidence of advanced neoplasia (advanced adenoma or CRC) in the control and intervention groups.

Secondary outcomes:Incidence of complications from colonoscopy (admissions for bleeding or perforation, or death).Risk factors associated with advanced neoplasia including age, sex, family history of CRC, previous history of adenoma, number of prior colonoscopies.Cost-effectiveness of a modified surveillance frequency using interval FIT compared to standard surveillance practice.Acceptability to consumers of changes to the surveillance strategies and the variables that predict this attitude.

### Statistical analyses

#### Advanced neoplasia incidence

Colonoscopy outcomes of the intervention group will be compared to those from the control group. Incidence of advanced neoplasia (CRC and advanced adenoma), non-significant adenomas, non-neoplastic lesions, and normal outcomes will be compared between groups with univariate (Fisher’s exact and chi-squared test). Odds ratios will be calculated from logistic regression analysis to assess factors associated with the development of advanced neoplasia, adjusted for risk factors associated with neoplasia development such as age, sex, and the original surveillance interval. To account for non-adherence of the timing for the surveillance colonoscopy in the study arm (e.g., colonoscopy was brought forward due to a positive FIT or symptoms), alternative analyses will be incorporated such as per-protocol, modified intention-to-treat, or as-treated, alongside the primary intention-to-treat analysis.

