Screening using the non-invasive fecal immunochemical occult blood tests (FITs) for detection of fecal hemoglobin (F-Hb) shed from neoplastic lesions, with colonoscopy follow-up for those testing positive, can effectively reduce CRC incidence, severity, and mortality. This is through diagnosing cancers earlier and by detecting and removing the pre-cursor lesions [8]. FIT has a good sensitivity for detection of CRC at 65–87% [9], and the concentration of Hb in the feces is positively associated with risk of advanced neoplasia (advanced adenoma or CRC) [10]. This association has also been observed in individuals with Hb concentrations below the positivity threshold. In the Dutch national screening program, the risk of advanced neoplasia was significantly higher for individuals with fecal Hb concentrations just below the positivity threshold, compared to those returning a fecal Hb of 0 µg Hb/g feces [11]. This was also supported in their follow-up findings that analyzed multiple rounds of screening, where individuals with undetectable and low (< 2 µg Hb/g feces) concentrations of Hb in the feces had the lowest risk for advanced neoplasia [12]. Although these studies were performed in an average risk screening population, the FIT sensitivity for CRC in an elevated risk population is 80% with a specificity of 89% [13]. Taken together, these data suggest that fecal Hb concentrations from FIT completed before surveillance colonoscopy could be a suitable tool to inform postponement of colonoscopies in those who return a very low fecal Hb concentration, thereby reducing the demand on colonoscopy resources.

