Two-sample OC-Sensor FIT kits (Eiken Chemical Company, Tokyo, Japan) will be sent annually only to participants who are enrolled into the intervention arm, on their original guideline scheduled surveillance colonoscopy due date. Participants on a 5-year surveillance and with a 2-year delay will receive two FIT kits (1 each year). Participants on a 3-year surveillance will receive one FIT. The colonoscopy procedure will be performed on-time (control group — no FIT required) or on the delayed due date (Intervention group) if the interval FIT is negative (i.e., < 20 µg Hb/g feces). Any participants presenting with symptoms will be scheduled for colonoscopy as soon as possible regardless of trial intervention and will be withdrawn from the study. At the completion of the study and collection of all data, analysis will be performed to determine the primary and secondary outcomes.

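### A colonoscopy brought forward by a positive interval FIT is prescribed by the protocol yet labelled timing non-adherence, which could make the supporting per-protocol and as-treated analyses understate an excess of advanced neoplasia

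*Protocol article*

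**What the plan says.** Three parts of the protocol article bear on this.

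- **Conduct.** Under Study schedule, intervention participants have their colonoscopy "on the delayed due date (Intervention group) if the interval FIT is negative". Under Interval FIT Hb analysis, a positive result means that "the surveillance colonoscopy will be scheduled as soon as possible, and the delayed procedure date will be abandoned". The same section adds: "These participants will remain enrolled and complete the follow-up survey as dictated in the study schedule". Table 1 schedules interval FIT for the intervention arm only.
- **Endpoints.** The cost-effectiveness outcome describes the strategy under test as a "modified surveillance frequency using interval FIT compared to standard surveillance practice".
- **Analysis.** Under Advanced neoplasia incidence, the plan sets out to account for "non-adherence of the timing for the surveillance colonoscopy in the study arm (e.g., colonoscopy was brought forward due to a positive FIT"; symptoms are the second example in the same bracket. The means are alternative analyses "such as per-protocol, modified intention-to-treat, or as-treated, alongside the primary intention-to-treat analysis".

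The article does not define the per-protocol, modified intention-to-treat or as-treated sets.

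**The concern.** A participant who has a positive interval FIT and is then scoped early has done what the intervention arm asks. Calling this non-adherence invites the supporting analyses to drop that person, or to count the person as not delayed.

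The people affected are not a random subset. The Introduction says that "the concentration of Hb in the feces is positively associated with risk of advanced neoplasia (advanced adenoma or CRC", so those who turn positive should carry more advanced neoplasia than the rest of their arm. Controls have no interval FIT, so no matching group leaves the control arm. The selection rests on a result that arises after randomization and exists in one arm only.

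The trial asks whether delay is safe. If the supporting analyses show a smaller excess than intention-to-treat, a reader may take that as reassurance when part of it comes from the classification.

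**Working it through.** **The plan's own figure.** Inputs from the Sample size section: control rate 9%, difference 5 points, two-sided alpha 0.05, power 80%, pooled variance. The alternative is taken as 14%, because 9% against 4% would need only 381 per arm.

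n = [1.960·√(2·0.115·0.885) + 0.842·√(0.09·0.91 + 0.14·0.86)]² / 0.05² = (0.8843 + 0.3785)² / 0.0025 ≈ 638 per arm.

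Dividing by 0.95 gives 671.6, that is 672, the stated size. The article does not mention this 5% inflation; it matches the poor-preparation rate of about 5% given under Colonoscopy procedure. Without inflation, 672 per arm gives 82% power. So 9% against 14% is a fair base for the check.

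**Effect of the label.** Let f be the share of the intervention arm that turns FIT-positive, q their yield of advanced neoplasia, and p the true intervention-arm rate. Arms are of equal size and all controls are scoped on time.

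- Per-protocol, FIT-positives excluded: intervention rate = (p − f·q)/(1 − f), against 9%.
- As-treated, FIT-positives counted as on time: the same intervention rate, against (0.09 + f·q)/(1 + f).

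The documents give neither f nor q for this population. The upper f of 11% is the complement of the 89% specificity in the Introduction. The 23% yield is borrowed from the Sample size section. The 15% and 30% yields are assumptions with no source in the documents.

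True rates 14% against 9%, an excess of 5.0 points:

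| f | q | Intervention rate after removal | On-time rate, as-treated | Per-protocol difference | As-treated difference |
|---|---|---|---|---|---|
| 3% | 15% | (0.14 − 0.0045)/0.97 = 13.97% | (0.09 + 0.0045)/1.03 = 9.17% | +5.0 | +4.8 |
| 8% | 23% | (0.14 − 0.0184)/0.92 = 13.22% | (0.09 + 0.0184)/1.08 = 10.04% | +4.2 | +3.2 |
| 11% | 30% | (0.14 − 0.0330)/0.89 = 12.02% | (0.09 + 0.0330)/1.11 = 11.08% | +3.0 | +0.9 |

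True rates 9% against 9%, with f = 5% and q = 23% (about 34 of 672 people, 7.7 of them with advanced neoplasia): the intervention rate becomes (0.09 − 0.0115)/0.95 = 8.26%, a per-protocol difference of −0.7 points. The as-treated on-time rate becomes (0.09 + 0.0115)/1.05 = 9.67%, a difference of −1.4 points. Delay would look slightly beneficial through classification alone.

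**Direction.** The per-protocol rate falls below p only if q exceeds p. The as-treated comparator rises only if q exceeds 9%.

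**With FIT-triggered colonoscopy classed as adherent.** Nobody is moved for this reason, and the differences stay at +5.0 and 0.0 points.

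**The case against.** The strongest reply is that intention-to-treat is primary. It counts FIT-positive participants where they were randomized, and the article keeps them enrolled. That stands: a reader might infer that the main safety result is biased, and it is not.

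Second, the supporting sets are undefined, and such definitions are commonly left to an analysis plan that is not shown. A per-protocol set could still count a FIT-triggered colonoscopy as compliant. This stands in part: exclusion or reassignment is an inference. But the label is in the text, and handling the events so labelled is the stated purpose of these analyses.

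Third, the label speaks of timing, not of a protocol breach. The Objective concerns delay by 1 to 2 years, Table 1 puts the first interval FIT at month 0, and a colonoscopy within 6 months of the set time counts as appropriate. Someone positive at the first FIT and scoped promptly may have had no real delay. Wanting an analysis of people actually delayed is legitimate. It does not, however, isolate the effect of delay: it compares a subset selected on a negative FIT with unselected controls. The endpoint that names interval FIT is the cost-effectiveness one, so the case rests mainly on the conduct sections.

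Fourth, the inputs are weak. The 89% specificity is quoted alongside sensitivity for CRC, while participants here were selected for Hb below 2 µg/g. The 23% belongs to a far lower Hb cut-off than the 20 µg/g trigger. The true share and yield could lie either side of the values used.

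It is also tempting to say that the supporting analyses are bound to favour delay, or that agreement between per-protocol and intention-to-treat is this trial's main reassurance. The documents support neither. The direction depends on the yield, and the plan gives the per-protocol analysis no co-primary or decision role.

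**Conclusion.** The point holds, limited to the supporting analyses. The conduct sections prescribe an event that the analysis section calls non-adherence; this is a contradiction in the text, not a missing detail. If per-protocol and as-treated sets follow the label in the usual way, they understate an excess whenever FIT-positive yield exceeds the arm average, which the article's own statement on fecal Hb makes likely.

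The size ranges from nothing visible to most of the design difference in the as-treated analysis. That range rests on assumed positivity and yield and on inferred set definitions, so it shows what could happen and is not a forecast.

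A separate inconsistency sits in the same sentence. The Study schedule section withdraws participants who present with symptoms, whereas the analysis section treats a colonoscopy brought forward by symptoms as non-adherence to be analysed.

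**What to change.** In the Advanced neoplasia incidence section:

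- Class a protocol-directed colonoscopy after a positive interval FIT as adherent, and keep the participant and the findings in the intervention arm in the per-protocol and modified intention-to-treat sets.
- Limit non-adherence to timing departures that the protocol does not prescribe, such as a declined delay, or an early or late colonoscopy without a trigger.
- Label any as-treated analysis exploratory and confounded.
- Separately, reconcile the handling of symptomatic participants between the Study schedule and analysis sections, so that their status in each analysis set is clear.

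The cost is a change to analysis-set definitions, best made before outcome data are seen. The FIT reclassification needs no new data, no change in sample size and no change in conduct.

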#### Cost analysis

Health economic evaluation will be conducted from both societal and health sector perspectives using a cost-utility analysis (CUA), which involves estimating the incremental costs and effectiveness of extending colonoscopy surveillance intervals based on FIT Hb concentration versus current common practice. The effectiveness will be measured by using quality-adjusted life years (QALYs). An incremental cost-effectiveness ratio (ICER) will be calculated, and results will be plotted on a cost-effectiveness plane. A cost-effectiveness acceptability curve will provide information about the probability that the proposed strategy is cost-effective. The within trial analysis will then be extrapolated using a Markov model, which will consist of health states that are a consequence of the surveillance program, to capture the long-term cost-effectiveness of including FIT within a surveillance program to extend colonoscopy intervals. The lifetime estimates of effect on survival, quality of life, and costs will be estimated from a comprehensive literature review. Both costs and benefits will be discounted at 5% in the base model, in line with government policy.

#### Consumer acceptability

Overall preference for and satisfaction with surveillance type and frequency scenarios will be assessed by direct questions and the DCEs, giving different scenarios of methodology (colonoscopy with or without FIT), frequency, and effectiveness. Themes analyzed include (1) how acceptable they find a modified protocol, (2) how likely they would be to comply with it, and (3) how anxious the changes would make them. The collected demographic and clinical variables will be used to determine if there are any associations with surveillance preferences, and these will include: sex, age, number of previous colonoscopies, number of previous FITs, risk level for CRC (i.e., family history or previous adenoma), time since previous colonoscopy, or FIT. Individual differences in psychological measures will be collected to identify any measures that are likely to predict surveillance preferences: fear of cancer, quality of life, trust in healthcare, perceived convenience of FIT versus colonoscopy, dissatisfaction with previous procedures, relative differences in perceived response efficacy between the two, anxiety about change, and consumer health activation, and self-efficacy for FIT and colonoscopy. Health activation measurement will be with the Consumer Health Activation index (CHAI) [39] which comprises 10 items designed to assess a consumer’s health activation level, where high health activation is positively associated with health self-management [25]. An independent samples *t*-test will compare satisfaction between subjects offered the extended or standard surveillance protocol. A multivariable logistic regression analysis will be applied to determine predictors of preferences for surveillance type and frequency. Independent variables that are not linear on the log-odds scale will be categorized or transformed.

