After obtaining informed consent, all individuals will be sent two surveys (survey 1 and survey 2) by mail prior to them being informed of their randomization (Table 1). Survey 1 will establish baseline quality of life (QOL) using the validated EQ-5D instrument [35] and assess consumer preferences for surveillance strategies and health and psychological predictors of attitude to different protocols. Survey 2 will explore consumer preferences for test attributes using discrete choice experiments (DCE). Upon return of surveys 1 and 2, all participants will be sent a letter by mail informing them of their randomization arm. For those participants who are randomized to the intervention arm, a letter will be sent to their primary health care physician informing them of the change to their patients’ surveillance colonoscopy timing. The QOL survey will be repeated 4 weeks after the participant completes their colonoscopy (survey 3), along with completion of a costings survey (survey 4) within 2 weeks after colonoscopy to determine the costs (direct and indirect) involved with undergoing surveillance (such as time off work, transport costs, support person’s costs, out-of-pocket expenses for colonoscopy, cost of adverse events). Each survey will take less than 20 min to complete. Within the follow-up test preference and QOL survey (survey 5), which is provided one month after colonoscopy, there will also be questions to ascertain satisfaction with the surveillance procedure that they just completed. Finally, a follow-up DCE survey (survey 6) will repeat the DCE survey performed before colonoscopy, once the patients have been informed of pathology findings from their colonoscopy.

**Table 1 Tab1:** Study schedule listing the timing of events (in months) relative to the guideline recommended colonoscopy due date specified at the time of enrolment

	**Screening/enrolment**	**Survey 1 and survey 2**	**Randomization**	**On-time colonoscopy**	**FIT 1**	**FIT 2**	**Delayed colonoscopy**	**Survey 5**	**Survey 6**
Control	− 6	− 3	− 2	0	N/A	N/A	N/A	7	8
Intervention: 3-year surveillance	− 6	− 3	− 2	N/A	0	N/A	12	13	14
Intervention: 5-year surveillance	− 6	− 3	− 2	N/A	0	12	24	31	32

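### The between-arm satisfaction comparison is an unadjusted t-test that leaves out the stratification factors and a related baseline measure: valid, but less precise than it could be at almost no cost

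*Protocol article*

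**What the plan says.** Consumer acceptability is a listed secondary outcome. In the statistical section on it, the only between-arm test named is an independent-samples t-test, which "will compare satisfaction between subjects offered the extended or standard surveillance protocol". No covariate is mentioned.

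The same section lists psychological measures to be collected, among them "dissatisfaction with previous procedures, relative differences in perceived response efficacy between the two". Their stated purpose is "to identify any measures that are likely to predict surveillance preferences". The only multivariable model in the section serves that purpose and not the satisfaction comparison: "A multivariable logistic regression analysis will be applied to determine predictors of preferences for surveillance type and frequency".

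On timing, the Study schedule section says survey 1 will "assess consumer preferences for surveillance strategies and health and psychological predictors of attitude to different protocols", and that surveys 1 and 2 are sent "by mail prior to them being informed of their randomization". Table 1 puts them at month −3 and randomization at month −2. Satisfaction is asked after colonoscopy, in survey 5: "questions to ascertain satisfaction with the surveillance procedure that they just completed".

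The Enrolment criteria section stratifies the 1:1 randomization by referring endoscopist, private or public hospital, and recommended interval. None of these enters the satisfaction comparison.

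**The concern.** How satisfied someone is with a surveillance procedure may well depend on how they felt about earlier ones, and on where, by whom and at what interval they are followed. Variation of this kind that is known before the arm is disclosed can be taken out of the error term. A t-test leaves it in, so the interval for the arm difference is wider than it needs to be. Factors used to balance the arms are normally carried into the analysis as well. If they predict the outcome and are left out, the standard error does not credit the balance that stratification created.

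At stake is the precision of one between-arm estimate for a secondary outcome. For advanced neoplasia the protocol does plan a regression that adjusts for age, sex and original interval. The satisfaction comparison has no equivalent.

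**Working it through.** **The plan's own figure.** The protocol gives no sample size, SD, target difference or correlation for satisfaction. Its only sample size is 672 per group for advanced neoplasia (Sample size section: control rate about 9%, difference 5 points, two-sided Z test with pooled variance, 80% power, alpha 0.05). Taking 9% against 14%, with mean 11.5%:

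n = [1.960·√(2 × 0.115 × 0.885) + 0.842·√(0.09 × 0.91 + 0.14 × 0.86)]² / 0.05² = 638 per group.

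Dividing by 0.95 gives 638/0.95 = 672. The 5% allowance is inferred from the poor-preparation rate in the Colonoscopy procedure section; the protocol does not say it was used. The 672 is borrowed below only as the number of people per arm. It was not chosen with satisfaction in mind.

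**Is the covariate usable?** Adjustment is safe if the measure precedes knowledge of the arm. The protocol does not state which survey carries the dissatisfaction measure. It calls it a psychological measure that may predict preferences, and it describes survey 1 as covering psychological predictors of attitude. Reading the two together places it in survey 1, before randomization in Table 1. This is an inference from matching wording.

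**Effect of adjustment.** Normal approximation, equal arms, SD = 1.

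- Smallest difference with 80% power under the t-test: (1.960 + 0.842) × √(2/672) = 2.802 × 0.0546 = 0.153 SD.
- A covariate with correlation rho to the outcome multiplies the residual variance by 1 − rho².
- Power for the same 0.153 SD: Φ(2.802/√(1 − rho²) − 1.960).
- Equivalent unadjusted size: 672/(1 − rho²) per group.

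The protocol gives no rho, so every row is an assumption:

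| rho | Residual variance | Detectable difference at 80% power (SD) | Power for 0.153 SD | Equivalent n per group |
|---|---|---|---|---|
| 0 (t-test) | 1.00 | 0.153 | 80.0% | 672 |
| 0.1 | 0.99 | 0.152 | 80.4% | 679 |
| 0.2 | 0.96 | 0.150 | 81.6% | 700 |
| 0.3 | 0.91 | 0.146 | 83.6% | 738 |
| 0.4 | 0.84 | 0.140 | 86.4% | 800 |
| 0.5 | 0.75 | 0.132 | 89.9% | 896 |

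If only 470 per group returned the survey (an assumed figure, 70% of 672), the benchmark would be 2.802 × √(2/470) = 0.183 SD and the power column would not change.

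With the stratification factors in the model, rho² is replaced by the share of variance explained by all covariates together. The protocol gives nothing from which to estimate their contribution, so none is counted here.

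**Chance imbalance.** The standard error of a baseline imbalance at 672 per group is √(2/672) = 0.055 SD. At rho 0.5 an imbalance of that size moves the unadjusted estimate by 0.5 × 0.055 = 0.027 SD.

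**The case against.** The strongest reply is that nothing is wrong with the t-test. Under 1:1 randomization it is unbiased and controls type I error, and its standard error already allows for chance imbalance. That stands. A reader might infer that the planned comparison is biased or invalid, and the documents do not support this.

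A second tempting reading is that dissatisfaction with earlier procedures is the baseline version of the survey 5 score, so that a correlation near 0.5, and a gain worth a third more participants (896 against 672), can be expected. The documents do not support this either. They give no instrument or scale for the measure, and earlier procedures are not the procedure just completed. By Table 1 the gap from survey 1 to survey 5 is 10 months in controls (−3 to 7) and 16 or 34 months in the intervention arm (−3 to 13, −3 to 31). The section also speaks of satisfaction with surveillance type and frequency scenarios, so identifying the tested variable with the survey 5 question is itself an inference. A low rho is quite possible, and below 0.3 the gain is under 4 points of power.

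Third, the benchmark of 0.153 SD is small and was chosen so that the t-test has exactly 80% power. By the same approximation, with 672 per group the t-test already has about 96% power for 0.20 SD, since Φ(0.20/0.0546 − 1.960) = Φ(1.71). The protocol names no satisfaction difference that matters, so it cannot be said that the comparison is short of power. This stands too.

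Last, covariates for a secondary survey outcome are often left to an analysis plan that is not shown here. This carries less weight, because the article does not leave the method open: it names a test that takes no covariates. Adjusted supporting analyses may still exist elsewhere.

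**Conclusion.** The point holds as a modest, nearly free improvement of low severity. The article commits to an unadjusted test for satisfaction while the trial stratifies on three factors and plans to collect a related measure. The cost of leaving these out is lost efficiency, not bias.

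On the 0.153 SD benchmark the gain runs from 0.4 points of power at rho 0.1 to 9.9 points at rho 0.5. Where the trial would fall in that range cannot be derived from the protocol. The conclusion rests on three assumptions: that the dissatisfaction measure is in survey 1, that the tested outcome is the post-colonoscopy satisfaction score, and that the two are correlated to some degree. If the last fails, almost nothing is gained, and at this sample size almost nothing is lost. The case for including the stratification factors does not depend on any of the three.

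**What to change.** In the Consumer acceptability section, make the main satisfaction comparison a prespecified linear model. The outcome is the post-colonoscopy satisfaction score. The terms are randomized arm, the survey 1 score for dissatisfaction with earlier procedures, and the stratification factors: surveillance interval, hospital sector, and endoscopist where numbers allow. Report the adjusted mean difference with its 95% CI, and keep the t-test as a sensitivity analysis. State in the same sentence that the dissatisfaction measure is taken in survey 1 and which satisfaction score is analysed, so that neither has to be inferred.

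The cost is a change of wording. No new data, visits or participants are needed. A simple rule for missing baseline scores must be added. Fixing the covariates now also avoids choosing them later in a trial whose participants and endoscopists know the arm.
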